**Design and methods::**

This is a historically controlled post-market multicenter study to determine the safety and efficacy of the Barricaid device when used in addition to primary lumbar discectomy in a US population. A total of 75 patients with large annular defects will receive the Barricaid device following lumbar discectomy at up to 25 sites in the US and will return for clinical and imaging follow-up at 4 weeks, 3 months, and 1 year. Trial oversight will be provided by a data safety monitoring board and imaging studies will be read by an independent imaging core laboratory. Patients treated with the Barricaid device in a previous European randomized trial with comparable eligibility criteria, surgical procedures, and outcome measures will serve as historical controls. Main outcomes will include back pain severity, leg pain severity, Oswestry Disability Index, health utility on the EuroQol-5 Dimension questionnaire, complications, symptomatic reherniation, and reoperation. Propensity score adjustment using inverse probability of treatment weighting will be used to adjust for differences in baseline patient characteristics between the US trial participants and European historical controls.

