## Introduction

1

Lumbar disc herniation is a localized displacement of disc material beyond the normal margins of the intervertebral disc space^[1]^ and is the primary cause of sciatica, which affects between 1% and 5% of the adult population each year.^[2]^ First-line treatments for sciatica are nonsurgical and may consist of physical therapy, pharmacologic therapy, and/or epidural steroid injection. Regardless of whether conservative treatment is undertaken, acute sciatica symptoms eventually subside in most patients.^[3,4]^ In patients whose symptoms are resistant to conservative treatments, lumbar discectomy may be considered. Surgery typically results in faster symptom relief than continued conservative care^[5]^ and this clinical advantage persists over longer term follow-up.^[1]^ Consequently, lumbar discectomy has emerged as one of the most commonly performed spinal surgeries.^[6]^

Among patients undergoing lumbar discectomy, recurrent disc herniation occurs in 7% to 18% of patients within 2 years.^[7–10]^ Symptomatic reherniation requires reoperation in nearly 80% of cases.^[11]^ Patients at highest risk for reherniation are those with an annular defect of at least 6 mm width at completion of the lumbar discectomy procedure.^[12]^ This high-risk patient population is easily identifiable by measuring the annular defect width with a Penfield probe or specialized measurement tools. Historically, there has been a considerable unmet therapeutic need in this high-risk patient population. Over the last several decades, multiple attempts at the development of techniques and technologies to repair annular defects have been met with limited success.^[13]^

A bone-anchored device intended to occlude large annular defects after lumbar discectomy (Barricaid, Intrinsic Therapeutics, Woburn, MA) received Food and Drug Administration approval in 2019 based, in part, on 2-year safety and efficacy results from a 554-patient randomized trial conducted in Europe.^[14]^ Due to potential regional differences in patient characteristics or surgical practices, it is important to confirm the generalizability of these results to patients in the United States (US). The purpose of this historically controlled post-market confirmatory study is to report the safety and efficacy of the Barricaid annular closure device when used in addition to a primary lumbar discectomy procedure in a US patient population.

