### Study design

2.1

This is a prospective, multicenter, single-arm, historically controlled, confirmatory study that will be performed at up to 25 sites in the US. Patient recruitment is planned to begin in February 2020. The total study duration is expected to be 1.5 years, with 6 months of patient recruitment and 1 year of follow-up. Patient outcomes in this US trial of the Barricaid device (US Barricaid) will be descriptively compared with those from the Barricaid arm of a European randomized controlled trial consisting of 276 patients (EU Barricaid Controls).^[14]^ Propensity score methods will be used to adjust for differences in baseline patient characteristics between the US Barricaid patients and EU Barricaid Controls. The trial was prospectively registered at ClinicalTrials.gov (NCT03986580) before first patient enrollment. Trial oversight will be provided by a data safety monitoring board and data will be routinely monitored for accuracy.

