### Propensity score adjustment

2.5

We anticipate that patients enrolled in the US Barricaid trial may differ from the EU Barricaid Controls with respect to certain baseline characteristics. Therefore, we will prospectively collect clinically relevant baseline variables including age, sex, body mass index, smoking history, level of herniation, average disc height, herniation type, back pain severity, leg pain severity, and ODI. We will also obtain patient-level data from the EU Barricaid Controls for these variables from the study sponsor. We will then calculate propensity scores using binomial logistic regression to estimate the probability that patients would be enrolled in the US Barricaid trial. Propensity score adjustment using inverse probability of treatment weighting (IPTW) will be used to control for potential baseline covariate imbalances between study groups, thereby providing unbiased estimates of average treatment effects. Compared with other methods of propensity score adjustment such as stratification, matching, or covariate adjustment, IPTW is preferable for the analysis of differences in proportions,^[20]^ which coincides with the planned primary endpoint analysis of this trial. We will verify the performance of the propensity score model by comparing the distribution of covariates between study groups before and after propensity score adjustment using the absolute average standardized difference (ASD) statistic. The ASD will be calculated as the difference in means or proportions between study groups divided by the pooled standard deviation. A negligible difference between treatment groups will be defined as an ASD of <0.1.^[21]^

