### Statistical analysis

2.6

Using a Clopper-Pearson exact test, a sample size of 75 patients (70 evaluable at 3 months) produces a 2-sided 95% confidence interval ranging from 0.4% to 10.2% when the symptomatic reherniation rate is 3.0%. The primary endpoint will be calculated as the number of patients who experience symptomatic reherniation through the end of the 3-month follow-up visit (postoperative day 105) divided by the sum of patients who return for the 3-month follow-up visit and all patients with confirmed symptomatic reherniation who fail to return for this visit. The propensity score-adjusted primary endpoint results will be descriptively reported for patients treated with the Barricaid device in each study, with no formal hypothesis testing. The difference in propensity score-adjusted 3-month reherniation risk between the US Barricaid trial participants and the EU Barricaid Controls will be reported as an absolute risk difference and 95% confidence interval.

Primary study results will be derived from propensity score-adjusted comparisons. Group comparisons without propensity-score adjustment will be performed as a sensitivity analysis. Baseline characteristics will be summarized with standard descriptive statistics. Categorical variables will be described with percents and counts. Continuous variables will be described with means and standard deviations, or medians and ranges. Longitudinal changes in patient-reported outcomes will be evaluated with a mixed model analysis of variance. Categorical efficacy data will be evaluated as the number of patients with an event divided by the number of patients with follow-up data plus the number of patients with an event who miss the follow-up visit. Symptomatic reherniation and reoperation rates will be evaluated in a sensitivity analysis using Kaplan–Meier time-to-event methods. Missing data imputation will not be performed.

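### The primary weights target a pooled sample that is about 79% European, which fits poorly with the aim of describing US performance and with the unweighted precision statement

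*Protocol article*

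**What the plan says.** Section 2.5 (Propensity score adjustment) of the protocol article fits a "binomial logistic regression to estimate the probability that patients would be enrolled in the US Barricaid trial" and applies IPTW to the resulting scores, "thereby providing unbiased estimates of average treatment effects". Balance is to be checked with standardised differences against a threshold of 0.1.

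Section 2.6 (Statistical analysis) reports the adjusted primary endpoint descriptively for each study and gives an adjusted risk difference with a 95% interval. It adds: "Primary study results will be derived from propensity score-adjusted comparisons". Unadjusted group comparisons are a sensitivity analysis, and nothing is formally tested.

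The Introduction gives the purpose as reporting safety and efficacy of the device "when used in addition to a primary lumbar discectomy procedure in a US patient population". The comparator is "the Barricaid arm of a European randomized controlled trial consisting of 276 patients (EU Barricaid Controls").

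The sample size is justified by precision: "Using a Clopper-Pearson exact test, a sample size of 75 patients (70 evaluable at 3 months") gives a "2-sided 95% confidence interval ranging from 0.4% to 10.2% when the symptomatic reherniation rate is 3.0" percent.

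**The concern.** Weights for an average treatment effect are 1/p for US patients and 1/(1-p) for EU patients, where p is the probability of being a US patient. They standardise both groups to the combined sample, which is mostly European here. The adjusted US incidence then estimates what US sites would see with a largely European case mix. The Introduction and the end of the Discussion ask about US patients as they are.

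Two consequences follow:

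- If case mix differs on prognostic factors, the adjusted US rate differs from the rate in the US patients. The Discussion proposes to read closeness to the EU rate as evidence of effectiveness in the US, so the choice of target population bears on how the result is interpreted.
- The largest and most variable weights fall on the smaller group, where about 2 events are expected (0.03 × 70 = 2.1). The precision used to justify 75 patients is then not the precision of the result labelled primary.

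The wording in section 2.5 also claims too much. Both groups receive the same device, so the contrast is a regional difference and not a treatment effect. Lack of bias would require no unmeasured confounding, adequate overlap and a correct propensity model.

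**Working it through.** **Inputs from the protocol article.** US patients: 75 enrolled, 70 evaluable at 3 months. EU controls: 276. Assumed rate: 3.0%. Section 2.5 lists ten baseline variables.

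**1. The plan's own interval.** Clopper-Pearson limits are the 2.5% quantile of Beta(x, n-x+1) and the 97.5% quantile of Beta(x+1, n-x). With n = 70 and x = 0.03 × 70 = 2.1 they are 0.39% and 10.16%, which reproduces 0.4% to 10.2%. (With a whole number of events, 2/70, they are 0.35% and 9.94%.) The stated figure is therefore for an unweighted proportion in 70 US patients.

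**2. Share of the target population.** 276/(75 + 276) = 276/351 = 78.6% European.

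**3. Shift of the adjusted US rate (assumed inputs).** Take a risk factor with prevalence 50% in the US and 25% in the EU, and event risks of 5% with it and 1.5% without.
- US case mix: 0.50 × 5% + 0.50 × 1.5% = 3.25%.
- Pooled prevalence: (75 × 0.50 + 276 × 0.25)/351 = 0.303. Rate: 0.303 × 5% + 0.697 × 1.5% = 2.56%, which is 0.69 points lower.
- Prevalences exchanged: the US case mix gives 0.25 × 5% + 0.75 × 1.5% = 2.38%. The pooled prevalence is (75 × 0.25 + 276 × 0.50)/351 = 0.447, giving 0.447 × 5% + 0.553 × 1.5% = 3.06%, which is higher.
- Equal prevalence: no shift.

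**4. Precision (simulation, assumed imbalance).** I simulated 75 US and 276 EU patients with ten independent normal covariates, each shifted by the same amount, and a fitted logistic propensity score (1,000 data sets per scenario, mean results). Effective sample size (ESS) = (Σw)²/Σw². The half-width of the risk-difference interval at 3% in both groups is 1.96 × √[0.03 × 0.97 × (1/ESS_US + 1/ESS_EU)], with US ESS multiplied by 70/75. Unweighted, it is 4.5 points.

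| Shift per covariate | US ESS, pooled target | EU ESS, pooled target | EU ESS, US target | Half-width, pooled target | Half-width, US target |
|---|---|---|---|---|---|
| 0 | 67 | 274 | 232 | 4.7 | 4.6 |
| 0.1 SD | 63 | 272 | 210 | 4.8 | 4.6 |
| 0.2 SD | 52 | 266 | 159 | 5.2 | 4.8 |
| 0.3 SD | 38 | 253 | 103 | 6.0 | 5.2 |

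With the US target the US group keeps its full 75 (70 evaluable). Before rounding, the gain in half-width is 0.13, 0.20, 0.43 and 0.79 points. Putting the pooled-target US ESS (× 70/75) into the Clopper-Pearson formula as an approximation, the upper limit for a 3% US rate becomes about 10.8%, 11.2%, 12.4% and 14.9%, against the stated 10.2%.

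**The case against.** Several objections have force.

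- **The pooled contrast is legitimate.** The Discussion gives the primary goal as finding whether US outcomes are comparable to those of the European trial. Standardising both groups to a common case mix is a valid way to do that. A reader might infer that the adjusted US rate is wrong, or says nothing about US patients. The documents do not support that: it is computed from US patients' outcomes and is valid for a different population.
- **The crude US rate survives.** Section 2.6 defines the primary endpoint as a simple count over a simple denominator, gives an exact interval for it, and keeps unadjusted comparisons as a sensitivity analysis. A reader might infer that the observed US rate is lost. More accurately, it is not what the plan calls primary.
- **The weights are inferred.** No formula is printed. The reading rests on IPTW together with the stated average treatment effect. Stabilisation, truncation and the variance method may be in the full plan and are not criticised here.
- **The size is assumed.** A reader might infer that the plan will understate US risk. No imbalance is reported, eligibility and technique are described as comparable, and the shift could be upward or nil. The loss from 75 to 67 comes from fitting ten covariates alone.
- **No decision rule depends on the choice.** Reporting is descriptive, and the precision gain is modest.

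These points lower the severity. They do not remove the mismatch. The protocol itself names the average-effect target, and the balance check shows only whether the groups resemble each other, not whether they resemble US patients.

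**Conclusion.** The point stands as a recommended improvement. On the natural reading of section 2.5, the result that section 2.6 calls primary describes a population that is about 79% European, while the Introduction and the end of the Discussion ask about a US one. The interval of 0.4% to 10.2% does not carry over to the weighted US rate.

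The 79% share and the source of the planned interval follow from the document's own figures. The rest depends on assumptions: equal shifts in ten independent normal covariates for the effective sample sizes of 67, 63, 52 and 38, and an invented risk factor for the rate shift of 0.69 points. A claim that the comparison is invalid, or that the plan must not proceed without this change, would go beyond what the document shows.

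**What to change.** In section 2.5, name the US population as the target of the primary weights: weight 1 for each US patient and p/(1-p) for each EU patient. The primary US incidence is then the observed rate with its Clopper-Pearson interval, as the sample-size statement assumes, and the EU rate is standardised to the US case mix. In section 2.6, describe the primary comparison in those terms and report the effective sample size of each weighted group. The pooled-target analysis may be kept as a sensitivity analysis.

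Replace the claim of unbiased average treatment effects with a statement that the regional difference is adjusted for measured baseline covariates only.

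The cost is wording in two sections and a changed weight formula, with no new data. The EU effective size falls to roughly 100 to 230 of 276 in these scenarios, but the risk-difference interval is still slightly narrower, by about 0.1 to 0.8 points in half-width.

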### Statistical analysis

2.6

Using a Clopper-Pearson exact test, a sample size of 75 patients (70 evaluable at 3 months) produces a 2-sided 95% confidence interval ranging from 0.4% to 10.2% when the symptomatic reherniation rate is 3.0%. The primary endpoint will be calculated as the number of patients who experience symptomatic reherniation through the end of the 3-month follow-up visit (postoperative day 105) divided by the sum of patients who return for the 3-month follow-up visit and all patients with confirmed symptomatic reherniation who fail to return for this visit. The propensity score-adjusted primary endpoint results will be descriptively reported for patients treated with the Barricaid device in each study, with no formal hypothesis testing. The difference in propensity score-adjusted 3-month reherniation risk between the US Barricaid trial participants and the EU Barricaid Controls will be reported as an absolute risk difference and 95% confidence interval.

Primary study results will be derived from propensity score-adjusted comparisons. Group comparisons without propensity-score adjustment will be performed as a sensitivity analysis. Baseline characteristics will be summarized with standard descriptive statistics. Categorical variables will be described with percents and counts. Continuous variables will be described with means and standard deviations, or medians and ranges. Longitudinal changes in patient-reported outcomes will be evaluated with a mixed model analysis of variance. Categorical efficacy data will be evaluated as the number of patients with an event divided by the number of patients with follow-up data plus the number of patients with an event who miss the follow-up visit. Symptomatic reherniation and reoperation rates will be evaluated in a sensitivity analysis using Kaplan–Meier time-to-event methods. Missing data imputation will not be performed.

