**Figure 2 F2:**
[figure not shown]
Algorithm to determine occurrence of symptomatic reherniation. AE = adverse event, HNP = herniated nucleus pulposus, MRI = magnetic resonance imaging, ODI = Oswestry Disability Index, VAS = visual analogue scale.

An independent imaging core laboratory will read imaging to assess device status and anatomical characteristics following the procedure. Key imaging variables will include Modic changes, Pfirrman grade, anterior and posterior ossification, spontaneous fusion, disc degeneration, herniation recurrence, annular tears/fissures, and device events such as device integrity, migration, and subsidence.

The primary endpoint of the study is the incidence of symptomatic reherniation through the 3-month follow-up visit. Secondary endpoints of the study will include symptomatic reherniation, reoperation, back pain severity, leg pain severity, ODI, and adverse events at 3 months and 1-year follow-up.

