The primary endpoint of this study will be evaluated at 3 months and patients will continue in follow-up for 1 year after surgery. Although it could be argued that longer follow-up is needed in this relatively young patient population, the 3-month primary endpoint analysis is justified since early clinical outcomes in this patient population are highly predictive of long-term recurrence risk. Using 3-year data from the EU Barricaid Controls, we developed a Cox proportional hazards model that included 15 variables including age, sex, body mass index, index level, smoking history, symptomatic reherniation by 3 months, back pain at baseline, back pain at 3 months, 3-month change in back pain, leg pain at baseline, leg pain at 3 months, 3-month change in leg pain, ODI at baseline, ODI at 3 months, and 3-month change in ODI. In multivariate analysis, symptomatic reherniation by 3 months and back pain severity at 3 months were independently associated with symptomatic reherniation risk at 3 years. Patients who were free from reherniation and with back pain scores under 13/100 at 3-month follow-up had a 3-year reherniation risk of 6.1%. In contrast, patients with early reherniation or 3-month back pain scores of 13/100 or higher had a 3-year reherniation risk of 22.6%. Additionally, the 1-year follow-up duration is clinically justified; among patients with a symptomatic reherniation through 3 years following Barricaid treatment, 60% were identified within the first year.^[26]^ Lastly, clinical outcomes during the first year after surgery are important metrics utilized by healthcare payers for making coverage decisions on new medical technologies. Another potential criticism of this study is a sample size of only 75 patients. This sample size was determined by calculating the minimum number of patients that would provide sufficient precision around the primary endpoint estimate. While formal noninferiority testing with patients in the US Barricaid Trial and the EU Barricaid Controls would have been preferable, such a study would be impractical since a sample size of over 1000 patients would be required to provide sufficient statistical power.

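### The only stated precision (0.4% to 10.2%) is for the unadjusted US rate, but the primary results are weighted rates and a weighted US-minus-EU risk difference

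*Protocol article*

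**What the plan says.** Section 2.6 gives the sample-size rationale. It names the Clopper-Pearson method, plans for 75 enrolled and 70 evaluable, and reports that this "produces a 2-sided 95% confidence interval ranging from 0.4% to 10.2% when the symptomatic reherniation rate is 3.0" percent. This is an interval for one binomial proportion in the US patients. The Discussion describes how the number was reached: "This sample size was determined by calculating the minimum number of patients that would provide sufficient precision around the primary endpoint estimate".

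The primary endpoint is defined in section 2.4: "The primary endpoint of the study is the incidence of symptomatic reherniation through the 3-month follow-up visit". How it is analysed is set out elsewhere:

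- Section 2.5 chooses inverse probability of treatment weighting because "IPTW is preferable for the analysis of differences in proportions", and says that this matches the planned analysis of the primary endpoint.
- Section 2.6 states: "Primary study results will be derived from propensity score-adjusted comparisons". Comparisons without adjustment are a sensitivity analysis.
- Section 2.6 also says that the adjusted difference in 3-month risk between the US patients and the EU controls "will be reported as an absolute risk difference and 95% confidence interval".

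No precision is given for the weighted US rate or for the weighted risk difference.

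**The concern.** When a study has no hypothesis test, its sample size is justified by the precision of the estimate that it will report as primary. Here the justification is worked out for a different estimate, the crude US proportion. Two sources of variance are left out. Weighting reduces the effective number of US patients, and a difference from the European controls adds their sampling error.

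This matters because of the weight that the Discussion puts on the comparison. It gives the primary goal as finding out whether US outcomes are comparable with the European ones. It also says that US recurrence rates close to the European ones would be sufficient evidence of effectiveness in US patients. A reader weighing that statement needs the expected interval for the adjusted rate and the adjusted difference, and the article gives neither.

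**Working it through.** **Inputs from the article.** 70 evaluable US patients, assumed rate 3.0%, two-sided 95%, Clopper-Pearson (2.6); 276 EU controls (2.1); ten baseline covariates in the propensity model and weighting for average treatment effects (2.5).

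**Inputs assumed here.** A 3-month EU rate of 3%, and the size of the baseline imbalance. The article gives neither.

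**1. The stated figure.** Clopper-Pearson limits are the 2.5% quantile of Beta(x, n−x+1) and the 97.5% quantile of Beta(x+1, n−x). With n = 70 and x = 0.03 × 70 = 2.1, they are 0.39% and 10.16%, which is the stated 0.4% to 10.2%. It therefore reproduces as an unweighted one-sample interval. For whole counts:

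- 2/70 (2.86%): 0.35% to 9.94%
- 3/70 (4.29%): 0.89% to 12.02%

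**2. Unweighted risk difference.** Half-width = 1.96 × √[p(1−p)(1/70 + 1/276)] with p(1−p) = 0.03 × 0.97 = 0.0291. This is 1.96 × √[0.0291 × (0.01429 + 0.00362)] = 4.47 points. With an EU rate of 2% or 5% it is 4.3 or 4.8 points. If only 250 EU patients are evaluable, it is 4.5 points. A Newcombe interval for 2/70 against 8/276 runs from about −3.5 to +7.1 points.

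**3. Weighted results.** I simulated ten independent standard normal covariates, each shifted by d SD in the 70 US patients relative to the 276 EU patients. I fitted the logistic propensity model and formed weights 1/e (US) and 1/(1−e) (EU). The effective sample size in each group is (Σw)²/Σw², averaged over simulated data sets. These sizes replace 70 and 276 in step 2, and n = effective US size with x = 0.03n goes into step 1.

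| d (SD) | Effective US n | Effective EU n | Adjusted US rate, upper limit | Risk-difference half-width |
|---|---|---|---|---|
| 0.1 | 57.9 | 272 | 11.2% | 4.8 points |
| 0.2 | 47.4 | 267 | 12.6% | 5.3 points |
| 0.3 | 35.1 | 255 | 15.1% | 6.0 points |

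For d = 0.3: 1.96 × √[0.0291 × (1/35.1 + 1/255)] = 6.0 points.

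Fixed design effects give a cross-check. A US design effect of 1.5 or 2 (EU 1.1 or 1.2) gives half-widths of 5.3 and 6.1 points. An exact interval on 70/1.5 = 46.7 or 70/2 = 35 patients has an upper limit of 12.7% or 15.1%.

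The effective-sample-size formula is an approximation. It treats the weights as unrelated to outcome and gives no credit for covariates that predict outcome.

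**The case against.** The strongest defence is that the interval is correct for what it describes. The endpoint is defined as an incidence, section 2.6 sets out its numerator and denominator, and nowhere does the article say that the interval is for the risk difference. The between-study results are declared descriptive, and the Discussion concedes that a noninferiority comparison would need over 1000 patients. The stated interval also has a half-width of (10.2 − 0.4)/2 = 4.9 points, so the risk-difference half-width of 4.5 to 6 points is not dramatically larger. All of this is true, and it limits the point to a mismatch of estimates. It does not remove the mismatch, because the incidence reported as primary is itself weighted, and its upper limit rises above 10.2% under every imbalance examined.

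A reader might infer more, and the article does not support it:

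- *That 2.1 events is an arithmetic error.* Putting n × p into the formula is a common planning convention. Using 2/70 instead moves the upper limit by about 0.2 points, and this is not why the interval fails to describe the primary analysis.
- *That 75 cannot be a minimum because no target is printed.* A journal article may leave the target to the full protocol.
- *That the number was really set on feasibility.* Nothing says so. The remark about impracticality concerns a noninferiority study.
- *That the risk-difference interval will collapse if no US patient has an event.* This depends on the interval method, which the article does not name and may leave to the analysis plan.

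**Conclusion.** The point holds as a mismatch between the stated precision and the primary analysis. The interval of 0.4% to 10.2% is valid for the unadjusted US rate. It is not the precision of the weighted rate or of the weighted risk difference, and the Discussion's claim of sufficient precision rests on it.

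Under the assumptions above (3% in both groups, 70 against 276, ten independent normal covariates differing by 0.1 to 0.3 SD), the upper limit for the adjusted US rate is about 11% to 15%. The risk-difference half-width is about 4.8 to 6 points, larger than the 3% rate itself. The direction for the adjusted rate is firm, since unequal weights reduce the effective sample size. The amount depends on an EU rate and an imbalance that the article does not report. It would be wrong to conclude that the article misstates the interval or presents it as that of the US–EU difference.

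**What to change.** In section 2.6, say that the exact interval applies to the unadjusted US rate, and give it for whole counts: with 70 evaluable patients, 0.3% to 9.9% for 2 events and 0.9% to 12.0% for 3 events. Then add the expected precision of the primary results with the assumptions beside it. For example: with 3% in both groups, 70 against 276 patients and baseline differences of 0.1 to 0.3 SD on each of ten independent covariates, the upper 95% limit for the adjusted US rate is about 11% to 15%, and the half-width for the adjusted risk difference is about 4.8 to 6 points, against 4.5 without weighting. The sponsor holds the EU patient-level data, or can obtain them, and can replace the assumed 3% with the observed EU rate.

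In the Discussion, tie the sentence on sufficient precision either to the unadjusted rate or to these restated figures. If a precision target was used, state it. Do not substitute a feasibility rationale unless that was the actual basis.

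The change is to text only. Enrolment and the analysis stay as planned, and the cost is a less favourable stated precision.

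### The rate formula keeps visit-missers who had an event and drops those who did not, so attendance can move the reherniation rate and the US-EU difference; the shift is small at the planned attendance

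*Protocol article*

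**What the plan says.** All of the following is in the protocol article, section 2.6 (Statistical analysis), unless another section is named.

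- The primary numerator is "the number of patients who experience symptomatic reherniation through the end of the 3-month follow-up visit (postoperative day 105").
- It is "divided by the sum of patients who return for the 3-month follow-up visit and all patients with confirmed symptomatic reherniation who fail to return" for that visit.
- For categorical efficacy data in general, the denominator is "the number of patients with follow-up data plus the number of patients with an event who miss the follow-up visit". This rule therefore also reaches the 1-year secondary endpoints listed in section 2.4 (Outcomes).
- Planned precision rests on "a sample size of 75 patients (70 evaluable at 3 months"), giving a "2-sided 95% confidence interval ranging from 0.4% to 10.2% when the symptomatic reherniation rate is 3.0"%.
- The adjusted US-EU contrast "will be reported as an absolute risk difference and 95% confidence interval", "with no formal hypothesis testing".
- Kaplan-Meier is already planned for symptomatic reherniation and reoperation, as a sensitivity analysis. Missing data are not imputed.

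Section 2.4 gives three routes to a symptomatic reherniation: a finding at reoperation, MRI at an unscheduled visit prompted by symptoms, and MRI at a scheduled visit combined with clinical criteria or a related adverse event. The first two do not require the scheduled visit; the third does.

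**The concern.** Entry to the denominator depends on the outcome. Two patients both miss the 3-month visit. One has a reoperation that shows reherniation and is counted in numerator and denominator. The other does well and disappears from the rate, even if seen event-free at 4 weeks or confirmed event-free at 1 year.

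The main result is an absolute difference between a post-market US cohort and the device arm of an earlier European trial. If the two studies differ in attendance, each rate is shifted by a different amount and the contrast carries the gap. Section 2.5 (Propensity score adjustment) presents the weighting as giving unbiased effects, but weights built from baseline covariates do not undo selection on the outcome. There is no test or margin, and the Discussion bases its conclusion on whether US rates approximate the European ones, so the point estimates matter.

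**Working it through.** **Inputs from the article.** 75 enrolled and 70 evaluable, so 5/75 = 6.7% not evaluable; assumed 3-month rate 3.0%; 276 European controls.

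**Assumptions, not in the article.** Attendance in the European group, the share of non-attenders' events that is captured, the risk in non-attenders, and event timing. The 6.7% is read as the share missing the visit.

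**1. The plan's own figure.** Clopper-Pearson limits with 0.03 × 70 = 2.1 events in 70 are 0.39% and 10.16%, matching the stated 0.4% to 10.2%. The whole-number case 2/70 (2.86%) gives 0.35% to 9.94%.

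**2. What the formula estimates.** Let p be the true risk, m the share missing the visit (unrelated to the event), and q the share of non-attenders' events captured. Approximately,

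expected rate = [(1 − m)p + mpq] / [(1 − m) + mpq].

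With p = 3.0%:

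| Missed (m) | q = 1 | q = 0.5 | q = 0 |
|---|---|---|---|
| 6.7% | 0.0300/0.9353 = 3.21% | 0.0290/0.9343 = 3.10% | 3.00% |
| 10% | 0.0300/0.9030 = 3.32% | 3.16% | 3.00% |
| 20% | 0.0300/0.8060 = 3.72% | 0.0270/0.8030 = 3.36% | 3.00% |

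In patients: two events with five event-free patients missing gives 2/70 = 2.86%, against 2/75 = 2.67% of all enrolled.

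**3. The bias can reverse.** Suppose non-attenders have twice the attenders' risk and none of their events is captured. The formula then returns the attenders' risk, p/[(1 − m) + 2m]: 0.03/1.0667 = 2.81% at 6.7% missed and 0.03/1.2 = 2.50% at 20%.

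**4. Effect on the US-EU difference.** Equal true risks of 3.0%, all events captured:

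- equal attendance: 0
- US 6.7%, EU 2% missed: 3.21 − 3.06 = +0.15 points
- US 20%, EU 2% missed: 3.72 − 3.06 = +0.66 points
- US 6.7%, EU 20% missed: 3.21 − 3.72 = −0.51 points

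For scale, the unweighted 95% half-width of the difference is 1.96 × √(0.03 × 0.97/70 + 0.03 × 0.97/276) = 4.5 points.

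**5. One year, illustration only.** Assume an 8% risk and full capture. Then 5%, 15% and 20% missed give 0.08/0.954 = 8.39%, 0.08/0.862 = 9.28% and 0.08/0.816 = 9.80%. A true difference of zero appears as +0.9 points (15% v 5%) or +1.4 points (20% v 5%).

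**6. Does Kaplan-Meier do better?** Simulation with n = 75, true risk 3.0% and events uniform over 105 days:

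| Situation | Missed | Formula | Kaplan-Meier |
|---|---|---|---|
| Random dropout, events seen only before dropout | 6.7% | 3.10% | 2.99% |
| Same | 20% | 3.37% | 3.01% |
| All non-attenders' events captured, event-free ones censored early | 6.7% | about 3.2% | 3.10–3.18% |
| Same | 20% | about 3.7% | 3.33–3.51% |
| No non-attenders' events captured | 6.7% | about 3.0% | 2.89–2.94% |
| Same | 20% | about 3.0% | 2.66–2.86% |

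The ranges cover censoring at day 28 and at a random time up to day 105. Kaplan-Meier is close to the truth when events and event-free time are followed to the same last contact. It is not when one is followed longer than the other.

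**The case against.** The strongest reply is that the effect is negligible where it counts. At the plan's own attendance and rate it adds at most 0.21 points, beside an interval of 0.4% to 10.2% and a half-width of about 4.5 points for the difference. Reporting is descriptive, the Discussion describes follow-up methods in the two studies as comparable, and Kaplan-Meier is already there as a check. This stands as to size at 3 months. It does not remove the defect: the article gives no European attendance, and comparable methods do not guarantee equal attendance. The article also does not say that the Kaplan-Meier check is weighted or yields a risk difference. That detail may sit in a fuller plan and is not itself a fault, but the check cannot be taken to cover the primary contrast.

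A reader might infer that the rates are simply biased upward. The documents do not support that. The scheduled-MRI route to an event is closed to a patient who misses the visit, so some events in non-attenders may go unseen, and the bias then shrinks, vanishes or reverses.

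A reader might also infer that changing to Kaplan-Meier settles the matter. It does not do so alone: if late events are picked up while event-free patients are censored early, it removes only part of the bias.

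**Conclusion.** The point holds in a conditional form. The denominator is outcome-dependent by its stated definition, and weighting on baseline variables does not correct that. Upward bias follows to the extent that non-attenders' events are captured outside scheduled visits. With full capture and attendance unrelated to risk, it is about 0.2 points at 3.0% risk and 5/75 missing, and about 0.7 points at 20% missing. Any shift in the US-EU difference needs unequal attendance or unequal event capture.

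It is tempting to conclude that the 1-year contrast will be off by about a point. The figures of +0.9 and +1.4 rest on an assumed 8% risk, assumed attendance in both groups and full capture. None of these is in the article, so they show sensitivity and are not a prediction. Nor do the documents support a claim that the 3-month primary result would be materially misleading at the planned attendance. The case for change is that the rule is avoidable, its effect depends on figures not yet known, and the better alternative largely builds on an analysis already planned.

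**What to change.** 1. Count patients confirmed event-free at a later contact as event-free at 3 months, using the same definition of confirmation in both studies.
2. Estimate the day-105 and 1-year risks, and their US-EU difference with a 95% confidence interval, by Kaplan-Meier weighted by inverse probability of treatment in both groups.
3. State one rule for both studies: censor at the last contact with known event status, and treat events learned of after that contact in the same way in each.
4. Keep the present ratio as a sensitivity analysis, and report attendance at each visit by group so that readers can judge how far it could have moved.

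Cost: event and last-contact dates are needed in both data sets, including the European patient-level data. The weighted Kaplan-Meier difference and its interval are slightly more work than a ratio of counts. The method still assumes non-informative censoring, which should be stated with the result.
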